#### Secondary outcomes and definitions

Secondary endpoints will include:
Neurologic injury is divided into two major categories: temporary neurologic dysfunction (TND) or TIA and permanent neurologic dysfunction (PND) or stroke
TND or TIA—neurologic symptoms lasting < 24 h and without evidence of infarction
i.Neurological imaging has to be normal with resolution of all symptoms within 24 hPND or stroke—presence of either new focal (embolic stroke) or global (diffuse coma) deficits which persist for longer than 72 h
i.Positive radiographic evidence of infarction in the appropriate territory

In the event of a suspected neurological injury the clinical team will be alerted and the study neurologists will be consulted. Neurologic injury will be quantified using a combination of validated cognitive screening tests and neurologic imaging. Screening tests will be performed preoperatively and on postoperative days 2 ± 2, 6 ± 1 (or prior to discharge), and 60 ± 14 by trained personnel (study coordinator, study neurologist, study nurse practitioner). Note both BI and MRS scores will only be performed postoperatively in the event of a postoperative stroke and will occur at the same times as the follow up NIHSS/MOCA testing. These points in time have been chosen based on previous studies [26] that actively monitor for stroke post-cardiac surgery, as well as to allow for long-term follow up of patients post-stroke. Screening tests include:

c.The National Institutes of Health Stroke Scale (NIHSS)—highly predictive of hospital disposition and long-term stroke outcomes. Scores range from 0 to 42. It has been shown for each one-point increase in NIHSS, the likelihood of going home is significantly reduced [27–29]
i.0 = no strokeii.1–4 = minor strokeiii.5–15 = moderate strokeiv.15–20 = moderate/severe strokev.21–42 = severe strokevi.Study neurologists following serial NIHSS scores will determine whether there was a change in examination from previous exams and whether this change was because of a suspected stroke
For the purpose of this study, severe strokes are defined as NIHSS ≥ 10 [26]Clinically significant strokes are defined as a change in NIHSS ≥ 4
This is based on data which show NIHSS scores < 6 indicate a strong likelihood of hospital discharge, with good recovery, and no long-term deficits [28, 30]d.The Montreal Cognitive Assessment (MOCA)—highly sensitive in detecting executive dysfunction. Scores range from 0 to 30 [31]
i.Scores > 26—no cognitive impairment (normal exam)ii.Scores < 26—mild cognitive impairmente.Modified Rankin Scale (MRS)—only to be used in the event of a postoperative stroke. The MRS is a reliable and reproducible scoring method for the assessment of deficits post-stroke in patients. Scores range from 0 to 6 [32, 33]
i.0, no symptomsii.1, no significant disability: able to carry out all usual activities, despite some symptomsiii.2, slight disability: able to look after own affairs without assistance, but unable to carry out all previous activitiesiv.3, moderate disability: requires some help, but able to walk unassisted.v.4, moderately severe disability: unable to attend to own bodily needs without assistance, and unable to walk unassistedvi.5, severe disability: requires constant nursing care and attention, bedridden, incontinentvii.6, deadf.Barthel Index of Activities of Daily Living (BI)—the BI is formed by several disability indexes and is a reliable and reproducible scoring method for the assessment of activities of daily living (ADLs) post-stroke in patients. Scores range from 0 to 20 [34–36]
i.Lower scores indicate increased disabilityii.When used to measure improvement after rehabilitation, changes of more than two points in the total score reflect probable genuine changeiii.Change on one item from fully dependent to independent are also likely to be genuine
2.Incidence of acute kidney injury (AKI)
Postoperative AKI will be assessed using the KDIGO criteria [37–39] and are summarized in Table 1Creatinine measurements will serve as the main indicator for assessing AKIAll those with KDIGO stage 1 or higher AKI will be considered to have sustained postoperative AKICreatinine measurements will be performed with routine bloodwork on POD 0, 1, 2 ± 2, 4 ± 1, 6 ± 1, and 60 ± 14 daysUrine output for the diagnosis of AKI will only be measured in the immediate postoperative period (48 h)Blood urea nitrogen (BUN) levels will also be obtained on the same days

**Table 1 Tab1:** KDIGO classification of AKI

Stage	Serum creatinine	Urine output
1	1.5–1.9 times baseline or ≥ 0.3 mg/dl (26.5 μmol/l) increase	< 0.5 ml/kg/h for 6–12 h
2	2.0–2.9 times baseline	< 0.5 ml/kg/h for ≥12 h
3	3.0 times baseline or Increase in serum creatinine to ≥ 4 mg/dl (353.6 μmol/l) or initiation of renal replacement therapy	< 0.3 ml/kg/hr. for ≥24 h or Anuria for ≥ 12 h3.Incidence of delirium
Delirium—reversible postoperative delirium lasting more than 48 h without localizing signs
i.Delirium assessment will be performed using CAM
For a diagnosis of delirium by CAM, the patient must display:
Presence of acute onset and fluctuating course ANDInattentionAnd either one of:
Disorganized thinking ORAltered level of consciousnessii.Assessments will be performed on POD 2 ± 2 and 6 **±** 14.Death
All cause postoperative 60-day or in-hospital mortality5.Cardiopulmonary bypass (CPB) time (minutes)6.Bleeding rates to qualify for mediastinal re-exploration
Indication for exploration defined as postoperative mediastinal bleeding of [40, 41]:
i.500 ml in any one hourii.1000 ml in any 4-h periodiii.Or at surgeons discretion7.Incidence and quantity (number of units/patient) of perioperative blood transfusions
Defined as all intraoperative and postoperative transfusions up to POD 7 or discharge (whichever comes first)The transfusion of packed red blood cells (pRBCs) will adhere to the previously defined transfusion trigger strategy whenever possible without compromising patient safety
i.A liberal transfusion threshold of Hb < 95 g/L will be used intraoperatively and in the ICU, while a Hb < 85 g/L will be adhered to after transfer to the wardNumber of platelets, fresh frozen plasma (FFP), and cryoprecipitate will also be tabulated for the same time period
i.No transfusion triggers given and left to discretion of caring physician8.Prolonged mechanical ventilation
Defined as those requiring ≥ 48 h of mechanical ventilationMeasured in hours from time of admission to the ICU9.Perioperative myocardial infarction
Clinically diagnosed using a combination of electrocardiographic (new Q wave on 12 lead ECG) and biochemical (troponin I > 45 ng/L) markers or both10.Length of stay
ICU hoursHospital days11.Quality of life (SF-12) survey
A measure of perceived health (health-related quality of life) that describes the degree of general physical health status and mental health distress [42]Will be assessed preoperatively and on POD 60 ± 14

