**Methods/design:**

This is a prospective multi-center, single-blind two-arm RCT comparing mild (32 °C) versus moderate (26 °C) hypothermic cardiac arrest in patients (*n* = 282) undergoing hemiarch surgery with antegrade cerebral perfusion (ACP). The primary endpoint is a composite of neurological injury (incidence of transient ischemic attack and/or stroke) and Kidney Disease Improving Global Outcomes (KDIGO) stage 1 or higher AKI. Secondary outcomes include death, cardiopulmonary bypass time, bleeding, transfusion rates, prolonged mechanical ventilation, myocardial infarction, length of stay, and quality of life measures.

Patients will undergo 1:1 block randomization to each treatment arm on day of surgery. Sequence of operation will be at the surgeon’s discretion with mandatory guidelines for temperature and ACP administration. Perioperative management will occur as per enrolling center standard of care. Neurocognitive function will be assessed for neurological injury using validated neurological screening tests: NIHSS, MOCA, BI, and MRS throughout patient follow-up. Diagnosis and classification of AKI will be based on rising creatinine values as per the KDIGO criteria. Study duration for each patient will be 60 ± 14 days.

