## Background

Thoracic aortic disease (TAD) is a silent epidemic affecting 15,000 people per year, with up to 45,000 deaths per annum in the United States, making it one of the leading causes of death in people over 65 [1]. New studies have shown an increased prevalence and incidence of TAD, with surgery remaining the only viable life-saving treatment [2, 3]. However, the way in which these surgeries must be conducted carries substantial risk of morbidity and mortality.

When surgery on the aortic arch is required, the necessity of stopping systemic blood flow to provide a clear operative field places perfusion-sensitive organs, such as the brain and kidneys, at significant risk of ischemic injury. Surgery on the aortic arch was only made possible in the mid-1970s, with the introduction of deep hypothermic cardiac arrest (DHCA) by Griepp et al. [4]. The concept of deep hypothermia to reduce oxygen and metabolic requirements of hypoxic tissue is well documented [5, 6], but it is not achieved without its own adverse effects on body homeostasis and processes, including longer cardiopulmonary bypass (CPB) times, increased coagulopathy, multi-organ dysfunction, systemic inflammatory response (SIRS), endothelial dysfunction, and neuronal apoptosis [7–11]. Unfortunately, these drawbacks are intimately associated with worse neurologic (transient ischemic attack (TIA) and stroke) and renal outcomes, which often result in debilitating and lifelong illnesses for patients.

Strokes post-cardiac surgery have been shown to double the duration and costs of hospitalization, and are associated with a five- to tenfold increase in early mortality, while up to 69% of survivors suffer severe physical disability, often requiring continuing care, rehabilitation, or placement in long-term care facilities [12]. Similarly, postoperative kidney injury can result in the need for permanent dialysis, requiring on-going hospital visits and substantial increases in mortality and morbidity [13]. These postoperative complications result in significant added expenditures for the health care system. It has been estimated that the economic impact of stroke post-coronary revascularization (which carries a substantially lower risk of stroke than aortic surgery) exceeds $2 to $4 billion dollars annually worldwide [14]. Thus, it can be inferred that stroke would have a similar, if not higher, economic impact among patients undergoing aortic arch surgery.

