To mitigate neurological complications, Bachet and Kazui [15, 16] developed selective anterograde cerebral perfusion (sACP). By directly cannulating the axillary or innominate artery, uninterrupted physiologic cerebral perfusion to the brain could now be maintained in patients during periods of circulatory arrest. This afforded patients almost complete neurological protection during arch surgery, effectively changing total body hypothermic circulatory arrest to isolated lower body circulatory arrest. Despite these advances in surgical technique, these procedures still carry high mortality and morbidity risks, and may be related to the adverse effects of profound hypothermia [17]. In an attempt to negate these risks, a trend towards significantly warmer core body temperatures has emerged across cardiac centers with positive outcomes being observed [8, 12, 13].

Previous retrospective studies and large meta-analyses comparing deep (14.1–20 °C) and moderate (20.1–28 °C) hypothermic cardiac arrest (MHCA) during aortic arch surgery (with sACP) have shown no differences in hospital mortality, visceral organ protection, and neurologic outcomes [8, 18, 19]. It is believed that by performing these operations at even warmer temperatures (mild hypothermia, 28.1–34 °C) the aforementioned risks associated with DHCA and MHCA can be further mitigated. Multiple case studies examining outcomes post-aortic surgery with mild hypothermia have also revealed no significant differences in mortality, renal failure, and neurological injury; even showing benefits with reduced coagulopathies and in some studies decreased permanent neurological deficits [5, 8, 20, 21].

While retrospective and uncontrolled studies are numerous and suggest the safety of warmer arch surgery [8, 17, 18], there is significant parametric variability in these studies. The optimal temperature for hypothermic circulatory arrest remains unclear and is confounded by numerous variables that are also without consensus, including site of temperature monitoring, sACP cannulation site, sACP perfusion rates, rapidity of cooling/rewarming, and the determination of outcome data [5]. Furthermore, few studies directly compare outcomes of one strategy versus another, and no prospective randomized controlled trials (RCT) exist to guide such therapy [5, 20].

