#### Postoperative assessment and follow-up study visits

On postoperative days 2 ± 2 days, 6 ± 1 days, and 60 ± 14 patients, will undergo neurocognitive screening by trained personnel. NIHSS and MOCA examinations will be made at each time point (or prior to discharge for time point 6 ± 1 days). In the event a neurological deficit is identified during assessment and/or based on patient symptoms (focal/global, motor/sensory loss, or prolonged delirium/agitation), neurological imaging will be obtained using computed tomography (CT) head or diffusion-weight magnetic resonance imaging (DW-MRI). MRIs will be used only if symptom onset is acute in nature requiring rapid diagnosis. Patients will also undergo MRS assessment only in the event of a postoperative stroke. BI scoring will be performed preoperatively and postoperatively only in the event of a stroke. Quality of life measures will be assessed using SF-12 health survey and obtained preoperatively and at final follow-up at 60 ± 14 days (see SPIRIT Fig. 1).

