#### Primary outcome and definitions

The primary efficacy endpoint for this study will be a composite of neurologic injury and AKI that occurs at any time over the 60 ± 14 day study period. Definitions are defined in secondary outcomes below.

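### The imaging rule for permanent neurologic injury leaves primary haemorrhagic stroke outside the primary endpoint as written, and no listed outcome counts spinal cord deficits by arm

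*Protocol article*

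**What the plan says.** Under Primary outcome and definitions, the endpoint is "a composite of neurologic injury and AKI that occurs at any time over the 60 ± 14 day study period", and the reader is sent on for its components: "Definitions are defined in secondary outcomes below".

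Secondary outcomes and definitions, item 1, then gives the operative rule: "Neurologic injury is divided into two major categories: temporary neurologic dysfunction (TND) or TIA and permanent neurologic dysfunction (PND) or stroke".

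- The transient category covers symptoms of under 24 h, with normal imaging and full resolution in that time.
- The permanent category covers a new deficit lasting beyond 72 h, either focal (glossed as embolic stroke) or global (glossed as diffuse coma). It carries the imaging condition "Positive radiographic evidence of infarction in the appropriate territory".

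The abstract describes the same component more loosely, as "a composite of neurological injury (incidence of transient ischemic attack and/or stroke").

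Under Postoperative assessment and follow-up study visits, a deficit found on examination or suggested by symptoms leads to imaging: "neurological imaging will be obtained using computed tomography (CT) head or diffusion-weight magnetic resonance imaging (DW-MRI"). No spinal imaging is named.

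The Background says of selective antegrade perfusion that it has the result of "effectively changing total body hypothermic circulatory arrest to isolated lower body circulatory arrest".

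**The concern.** The definition is built around ischaemic brain events. Two other kinds of serious neurologic injury do not fit either category as worded: a primary intracranial haemorrhage, and a lasting spinal cord deficit.

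For haemorrhage, the detailed definition departs from the ordinary meaning of stroke used in the abstract. Two adjudicators could classify the same patient differently, one following the abstract and one following the imaging criterion.

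For the cord, the gap matters because of what is randomized. The trial compares temperatures during lower-body arrest. It counts one lower-body organ, the kidney, and the section on statistical consideration expects more AKI because of lower-body ischaemia. It has no defined count of injury to the cord. The stated ambition is to support guidelines on temperature management, and readers of those guidelines would expect such a count by arm.

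**Working it through.** **Step 1. Apply the definitions as written.**

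| Patient | Transient category | Permanent category |
|---|---|---|
| Focal deficit > 72 h, brain infarct on scan | No (duration, imaging) | Yes |
| Focal deficit > 72 h, intracranial haemorrhage, no infarct | No (duration, imaging) | No (no infarction) |
| Paraparesis > 72 h, normal head scan | No (duration) | No (no infarction shown) |
| Paraparesis > 72 h, cord infarct on imaging | No (duration, imaging) | Unclear: the infarction wording could cover it, the embolic-stroke gloss points away |
| Paraparesis resolved < 24 h, normal imaging | Yes if the category is read as any temporary dysfunction; no if read as cerebral TIA | No |

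**Step 2. Look for the two events elsewhere.** Secondary items 1 to 11 are neurologic injury, AKI, delirium, death, bypass time, mediastinal re-exploration, transfusion, ventilation, myocardial infarction, length of stay and SF-12. The only bleeding outcome is mediastinal. The list under Frequency and duration of follow-up names TIA and stroke and neither of these events. The Modified Rankin Scale and the postoperative Barthel Index are done only after a stroke, so a patient with a cord deficit would have no planned postoperative disability score.

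**Step 3. The plan's sample size.** Inputs from Sample size: 35% versus 20%, alpha 0.05 (taken as two-sided; not stated), power 80%, 5% loss.

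n per arm = (0.35×0.65 + 0.20×0.80) × (1.960 + 0.842)² / 0.15² = 0.3875 × 7.849 / 0.0225 = 135.2, so 136. Then 136 / 0.95 = 143.2, so 144 per arm and 288 in total. The stated 282 is close (288/282 = 1.02) and is not at issue here.

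**Step 4. Sensitivity of the primary comparison.** Evaluable per arm: 141 × 0.95 = 134. The documents give no rate for the omitted events, so a range is assumed for patients who otherwise have no composite event. New rates are 0.35 + 0.65r (moderate arm) and 0.20 + 0.80r (mild arm). Power is for the pooled two-proportion test.

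| Assumed r | Moderate vs mild | Difference (points) | Power |
|---|---|---|---|
| None (as planned) | 35% vs 20% | 15.0 | 78.8% |
| 1% mild only | 35% vs 20.8% | 14.2 | 73.9% |
| 2% mild only | 35% vs 21.6% | 13.4 | 68.5% |
| 2% both arms | 36.3% vs 21.6% | 14.7 | 75.9% |
| 1% moderate only | 35.65% vs 20% | 15.65 | 81.9% |
| 2% moderate only | 36.3% vs 20% | 16.3 | 84.7% |

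In the mild arm, 1% to 2% is 134 × 0.80 × 0.01 = 1.07 to 134 × 0.80 × 0.02 = 2.14 patients.

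**Step 5. How many cord deficits one arm might contain.** If the rate were 0.2% to 2% (again an assumption), 141 patients would yield 0.28 to 2.8 expected cases. The chance of at least one is 1 − 0.998^141 = 25% to 1 − 0.98^141 = 94%. The width of that interval simply reflects the tenfold range assumed. Even with a proper count, zero in 141 would rule out only rates above 1 − 0.05^(1/141) = 2.1% (one-sided 95%).

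**The case against.** **The exclusion is inferred, not stated.** Neither event is expressly ruled out. The definition says infarction in the appropriate territory, not infarction of the brain, so an imaged cord infarct might be admitted, and the abstract's plain word stroke could be read to include haemorrhage. This stands for the cord infarct, which is ambiguous. It does not rescue haemorrhage, because the operative definition makes infarction a condition.

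**The events would not be lost.** NIHSS is repeated at three postoperative time points, study neurologists are consulted on suspected injury, the adverse event form records each event and its seriousness, and a DSMB meets twice a year. A patient with KDIGO stage 1 or higher AKI is a composite event anyway. All of this stands. What is missing is correct endpoint classification and a prespecified comparison by arm.

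**The full protocol may say more.** An article condenses. Here, however, it states the duration and imaging criteria explicitly, and the problem lies in what they say.

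**Stronger readings that the documents do not support.**

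- A reader might infer that the plan conceals a harm of the warmer arm. No section mentions the spinal cord or ties cord injury to 32 °C. The Background reports no significant differences in neurological injury with mild hypothermia, and eligibility is limited to an anticipated arrest under 20 min.
- A reader might infer that omitting haemorrhage favours the colder arm. The Background phrase "longer cardiopulmonary bypass (CPB) times, increased coagulopathy" describes deep hypothermia, which neither arm uses. The Background does mention reduced coagulopathy with mild hypothermia, but nothing links temperature to intracranial bleeding, and known coagulopathies are excluded.
- A reader might infer that the rule counts transient cord injury and drops permanent injury. That needs the transient category read broadly and the permanent one narrowly. Read consistently, the mismatch is firm only for a permanent deficit without an imaged infarct.

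**Conclusion.** The point holds as a defect of definition. As written, a primary haemorrhagic stroke falls outside both neurologic categories, in conflict with the abstract's description of the component. A lasting cord deficit with a normal head scan also falls outside both and appears in no listed outcome.

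The effect on the primary result is probably small and its direction is unknown. At an assumed 1% to 2% in a single arm, power moves from 78.8% to between 68.5% and 84.7%, depending on the arm. At 2% in both arms it is 75.9%. These figures rest on assumed rates and a two-sided test, and concern only patients without AKI or another composite event. The case for change rests on correct classification of strokes and on a by-arm safety count for the cord, not on rescuing the primary analysis.

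**What to change.** 1. In Secondary outcomes and definitions, item 1, change the imaging condition for permanent dysfunction or stroke so that new infarction or haemorrhage qualifies. Apply it to all randomized patients, including those enrolled since March 2018, by adjudicators blind to arm.
2. Leave the composite otherwise unchanged. Add new spinal cord deficit (paraparesis or paraplegia) as a named secondary safety outcome, reported by arm in all randomized patients. The NIHSS leg items already collected can serve as the screen, and the study neurologists already consulted can classify the deficit. Name both events in the data list under Frequency and duration of follow-up.

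Cost: a wording amendment, one or two CRF fields, a blinded check of the records of patients already enrolled, and a few rare events added to the stroke count. Adding cord deficit to the composite itself after recruitment has begun would be harder to defend, which is why it is proposed as a separate outcome.

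### The two categories that define neurologic injury in the primary composite are not exhaustive: deficits of 24–72 h, and deficits under 24 h with an infarct, belong to neither

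*Protocol article*

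**What the plan says.** In the Protocol article, Primary outcome and definitions sets the endpoint as "a composite of neurologic injury and AKI that occurs at any time over the 60 ± 14 day study period" and adds: "Definitions are defined in secondary outcomes below". The abstract describes the neurologic part as "incidence of transient ischemic attack and/or stroke".

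Secondary outcomes and definitions, item 1, then states: "Neurologic injury is divided into two major categories: temporary neurologic dysfunction (TND) or TIA and permanent neurologic dysfunction (PND) or stroke". The two categories are:

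- **TND/TIA:** symptoms under 24 h and no infarction. A sub-item adds: "Neurological imaging has to be normal with resolution of all symptoms within 24" hours.
- **PND/stroke:** "presence of either new focal (embolic stroke) or global (diffuse coma) deficits which persist for longer than 72" hours. A sub-item adds: "Positive radiographic evidence of infarction in the appropriate territory".

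The same item has the study neurologists consulted when an injury is suspected. They judge whether a change on serial NIHSS reflects a suspected stroke. It also labels strokes as severe or clinically significant by NIHSS. Postoperative assessment and follow-up study visits allows CT or DW-MRI and says: "MRIs will be used only if symptom onset is acute in nature requiring rapid diagnosis".

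**The concern.** A binary primary endpoint needs a rule that gives every patient an answer. These two definitions cut on duration at two different points, 24 h and 72 h, and tie opposite imaging findings to each side. That leaves combinations of duration and imaging with no category.

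The patients concerned are candidates for the primary endpoint. A patient with a 48-hour deficit and a visible infarct would be neither a TIA nor a stroke. Either such patients count as having no neurologic event, which lowers the event rate and costs power, or someone decides case by case. The Statistical analysis section has the SAP written only once data collection is complete for all participants. A rule supplied at that stage would be set after the outcomes it governs have been recorded.

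**Working it through.** **Step 1. Classify each combination.** Cross three durations with two imaging results and apply both definitions as written, first taking the stroke imaging line as a requirement.

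| Duration of deficit | Imaging normal | Infarct on imaging |
|---|---|---|
| Under 24 h | TIA | neither |
| 24–72 h | neither | neither |
| Over 72 h | neither (conditional) | stroke |

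Four of six cells have no category. Three of them follow directly from the text: both 24–72 h cells, and under 24 h with an infarct. The fourth, over 72 h with normal imaging, is empty only if positive imaging is required for stroke.

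**Step 2. Look for text that assigns the empty cells.** The neurologists judge whether an NIHSS change reflects a suspected stroke, but nothing lets that judgement replace the duration and imaging conditions. The NIHSS cut-offs grade strokes and do not place unclassified cases. The abstract names only TIA and stroke, so there is no third category.

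**Step 3. Reproduce the planned sample size.** Inputs from Sample size: 35% v 20%, alpha 0.05 (taken as two-sided; the text does not say), power 80%, 5% loss, 141 per arm.

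- Unpooled: n = (0.35×0.65 + 0.20×0.80) × (1.960 + 0.842)² / 0.15² = 135.2, so 136 per arm. Then 136/0.95 gives 144, and 136×1.05 gives 143.
- Pooled: 138 per arm; 138×1.05 gives 145.

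These are within 3% of 141, so the planned number is not in question.

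**Step 4. Baseline power.** Evaluable per arm: 141×0.95 = 134. Power = Φ{[(p1−p2)√n − 1.960√(2p̄(1−p̄))] / √(p1(1−p1) + p2(1−p2))}. With p1 = 0.35, p2 = 0.20 and p̄ = 0.275:

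- numerator: 0.15×11.576 − 1.960×0.6315 = 0.499
- denominator: 0.6225
- power: Φ(0.801) = 78.9%

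**Step 5. Illustrate a loss of events.** The plan expects neurologic injury in 15–20%, AKI in 25% and an overlap of 5–10%. Both 15+25−5 and 20+25−10 give 35%. Neurologic-only events are therefore 35−25 = 10 points in the control arm. Let a share g of these be lost in both arms, with the relative risk held at 20/35 = 0.571. Control becomes 35−10g points, and mild becomes 0.571 times that.

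| g (assumed) | Control v mild | Power, 134 per arm | Evaluable per arm for 80% |
|---|---|---|---|
| 0 | 35.0% v 20.0% | 78.9% | 138 |
| 20% | 33.0% v 18.9% | 75.5% | 150 |
| 40% | 31.0% v 17.7% | 71.9% | 163 |

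No value of g can be derived from the documents.

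**The case against.** Several points can fairly be made for the plan.

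- **Nothing says uncovered cases are non-events.** The text calls these two major categories and brings in study neurologists for every suspected injury. This stands. A reader might infer that real strokes will be systematically scored event-free, but the document does not say so. It leaves these cases unassigned, and any of these patients with AKI meets the composite anyway.
- **The imaging line under stroke may not be mandatory.** The TIA line says imaging has to be normal, whereas the stroke line carries no such verb. A global deficit such as diffuse coma also fits poorly with infarction in a territory. This stands, so the gap above 72 h is conditional. The other gaps do not depend on it.
- **MRI is not shut out.** A reader might infer that suspected strokes will mostly be judged on CT. An acute postoperative deficit could meet the stated condition for MRI, so that inference is not supported.
- **Systematic ascertainment is kept.** Serial NIHSS and MOCA screening remains. Whether the 15–20% planning rate used a different event definition depends on a cited source that is not at hand, so a contradiction cannot be claimed.
- **No direction of bias is shown.** Neurocognitive testers are blinded, and the illustration loses the same share in both arms.

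None of this gives a category to a 24–72 h deficit or to a short deficit with an infarct. Nor is it detail that an article leaves to a fuller document: the definition is given here, and it fails for some primary events.

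**Conclusion.** The neurologic component of the primary endpoint is not exhaustively defined. Deficits of 24–72 h and deficits under 24 h with an infarct have no category. Deficits over 72 h with negative imaging have none if the imaging line is a requirement. This conclusion comes from the text alone and needs no assumption about frequency.

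The size is unknown. Power of about 76–72%, against about 79%, holds only if 20–40% of neurologic-only events are lost equally in both arms and the relative risk stays at 0.571. A larger loss can be constructed. If 40% of all neurologic events (0.40×17.5 = 7 points) were lost and every one were AKI-free, control would be 28% and power about 66%. That is an extreme case, and nothing in the documents supports it as an expectation. AKI carries 25 of the 35 planned points, which limits the effect on the composite.

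**What to change.** Make the endpoint categories exhaustive, for example:

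- **Stroke:** a new focal or global deficit of 24 h or more, or of any duration when imaging shows acute infarction.
- **TIA/TND:** a deficit under 24 h without infarction.
- **24 h or more with negative or missing imaging:** the study neurologists decide, blind to arm, whether the case is a stroke.
- **Permanent deficit:** keep the subset over 72 h with positive imaging as a descriptive category.

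State explicitly whether positive imaging is required for stroke. Fix the rule before any comparison by arm, without waiting for the SAP planned after data collection, and apply it to all patients, including those already enrolled.

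The cost is mainly wording, since imaging and neurologist consultation are already planned. There are two drawbacks. Events accepted without imaging confirmation are slightly less specific. Also, the article's list of collected data names no onset or resolution times, and recruitment began in March 2018, so symptom timing for earlier patients may have to come from source records.
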